#### Data analysis

Structural image analysis will be conducted with the cortical thickness and voxel based morphometry (VBM) analysis pipeline, CIVET (version 2.0) (http://www.bic.mni.mcgill.ca/ServicesSoftware/CIVET-2-0-0-Introduction. T1-weighted MRI images will be corrected for non-uniformity artifacts using the N3 algorithm, masked and registered into stereotaxic space, and then segmented into grey matter, white matter and cerebral spinal fluid using an advanced neural net classifier [61, 62]. The white and grey matter surfaces will be extracted using the Constrained Laplacian-based Automated Segmentation with Proximities algorithm [63]. The resulting surfaces will be resampled to a stereotaxic surface template to provide vertex based measures of cortical thickness. For each participant, cortical thickness will then be measured in native space using the linked distance between the two surfaces across 81,924 vertices and a 20 mm surface smoothing kernel will be applied to the data [64]. Statistical analyses will be performed using SurfStat (http://www.math.mcgill.ca/keith/surfstat/), a statistical toolbox created for MATLAB (The MathWorks, Inc., Nathan, MA, USA).

Diffusion images will be processed with FSL (FMRIB Diffusion Toolbox, http://www.fmrib.ox.ac.uk/fsl/). Motion artifacts and eddy current distortions will be corrected by using affine registration of DWI to the b0 image. Diffusion data will be registered to standard MNI152 space (2 mm isotropic) using a two-stage registration: rigid-body alignment and nonlinear transformation. A diffusion tensor model will be fitted for each voxel to estimate the principle fiber directions and calculate a fractional anisotropy (FA) map. Then, the probabilistic distribution of fiber orientations will be estimated using FSL’s BEDPOSTX with a maximum of 2 fiber directions per voxel [65]. The probabilistic tractography will be applied by sampling 10,000 streamline fibers per voxel within the seed region using FSL’s PROBTRACKX [66, 67].

Functional image analysis will be carried out using FSL (FEAT – FMRI Expert Analysis Tool). The following pre-processing steps will be applied: motion correction using MCFLIRT [68], non-brain removal using BET [69], and spatial smoothing with a Gaussian kernel of FWHM 6 mm. Time-series general linear model will be carried out using FILM with an autocorrelation correction [70]. At the first level, the following contrasts: anticipation/feedback of win and lose *vs* reference (MIDT) and successful and failed inhibition *vs* baseline (Stop-Signal Task) will be estimated for each participant. Group-level (second level) analysis will be carried out using a fixed effects model, by forcing the random effects variance to zero in FLAME (FMRIB’s Local Analysis of Mixed Effects) [71]. *Z* (Gaussianised T/F) statistic images will be thresholded using clusters determined by *Z* > 2.3 and a corrected cluster significance threshold of *p* = 0.05.

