### Neuroventure: neuroimaging add-on study

#### Participants

Neuroventure will focus on high-risk students with SS and IMP personality profiles as they contribute most to the prediction of early onset substance-related behaviors in adolescence [42]. Thus, a subsample from the Co-Venture Trial of 60 high SS (30 of whom will receive the intervention), 60 high IMP (30 of whom will receive the intervention) and 30 low-risk (low SS and low IMP will not be invited to participate in the interventions) Grade 7 students (50% girls) will be invited to participate in this neuroimaging study (Please refer to Fig. 1 for the consort diagram and to Fig. 2 for the actual recruitment data). An independent informed consent from parents and adolescents will be obtained for the present study. Exclusion criteria will include major neuro-developmental disorders (e.g., autism), uncorrectable visual impairment or hearing deficits, severe mental health problems (e.g., schizophrenia, bipolar disorder), uninterruptable central nervous system medication, and any magnetic resonance imaging (MRI) contraindications (e.g., pregnancy, braces, etc.).

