#### Statistical analyses

The main objectives of the statistical analyses will be to characterize differences for fMRI, cortical thickness, VBM, DWI and behavioral measures between high (SS and IMP) and low-risk youth, binge drinkers and non-drinker trajectory, and those assigned to the intervention or not (with and without exposure to alcohol) over time. Two- and three-way repeated measures analyses of covariance (ANCOVA) will be performed based on region of interest (ROI) scores with covariates such as age, socioeconomic status, pubertal stage, IQ, and other drug use. For cortical thickness and VBM only a-priori defined ROI will be used (i.e., prefrontal lobes, basal ganglia, limbic brain regions and corpus callosum), as previous studies have shown that alcohol affects these regions. For fMRI, we will conduct both exploratory and ROI analyses, and for the DWI data, the regions showing linear age trends in the fMRI analysis will be used as start/finish points for probabilistic tractography.

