The main strengths of the study are that (i) the selection, intervention and measurement models are highly time-sensitive, capturing critical periods (12–14 and 14–16 years of age) when personality endophenotypes translate to risk for binge drinking and when early intervention can produce preventative effects. Furthermore, (ii) this critical period appears to overlap with the age at which drinking onset is highly related to future drinking [73], and when important brain maturation occurs [10]. In addition, (iii) this research design is highly powered as our screening procedure, which is largely based on personality assessment at 12–13 years of age, identifies individuals, SS and IMP youth, for whom binge drinking is almost certain to develop within the next 12 months. Our previous research has shown that at 13 years of age, high SS and IMP adolescents have normal rates of drinking and binge drinking (around 40%), but experience a rapid rate of onset of binge drinking between 14 and 15 years of age, with approximately 95% reporting binge drinking at 15 years of age [34]. We will also be able to (iv) test critical questions on the causal pathway from premorbid risk markers to early onset drinking, disruptions in brain function and, in turn, addiction outcomes. Finally, by being embedded into a larger population-based 5-year longitudinal randomized controlled trial, we will be able to directly (v) test the generalizability of our sample and findings to the general population, which is unique for pediatric neuroimaging studies, which tend to involve highly selective clinical samples or families with high education and socio-economic characteristics.

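### The voxelwise group-level fMRI model sets between-participant variance to zero, so its Z values are too large and the stated cluster-corrected p = 0.05 is not supported

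*Protocol article*

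**What the plan says.** All of this is in the Methods of the protocol article.

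- **First level (Data analysis).** The reward-task and stop-signal contrasts "will be estimated for each participant". What passes upward is therefore one set of contrast estimates per person.
- **Second level (Data analysis).** "Group-level (second level) analysis will be carried out using a fixed effects model, by forcing the random effects variance to zero in FLAME".
- **Threshold (Data analysis).** The resulting "statistic images will be thresholded using clusters determined by *Z* > 2.3 and a corrected cluster significance threshold of *p* = 0.05".
- **Sample (Participants).** "60 high SS (30 of whom will receive the intervention), 60 high IMP (30 of whom will receive the intervention) and 30 low-risk".
- **Aim (Statistical analyses).** Differences are to be characterised "between high (SS and IMP) and low-risk youth, binge drinkers and non-drinker trajectory, and those assigned to the intervention or not". The test named there is a repeated measures ANCOVA on ROI scores.
- **Role of the maps (Statistical analyses).** "For fMRI, we will conduct both exploratory and ROI analyses". Regions with linear age trends in the fMRI analysis then define where tractography starts and finishes.

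The article describes no level above the second. It gives no mixed-effects or permutation alternative for the voxelwise maps, and it does not restrict their interpretation to the youths who were scanned.

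**The concern.** When the units entering a model are people, the standard error of a group mean or group difference has two parts: measurement error within each scan, and real differences between people in activation. Forcing the random-effects variance to zero keeps the first part and discards the second. The resulting map describes the particular youths scanned. It does not show whether other youths with the same risk profile would show the same pattern.

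The choice also sits badly with the rest of the article. The Scanning protocol section justifies the reward task partly by its sensitivity to individual differences, which is incompatible with zero between-person variance. The Sample size justification uses 118 error degrees of freedom, which equals 125 participants − 3 groups − 4 covariates. That error term lies between people, and the voxelwise maps as specified would not use it.

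At stake is the meaning of significance in the voxelwise fMRI maps. Cluster correction takes the Z map as its input and assumes that it has the right null distribution. If the Z values are too large, more voxels pass the cluster-forming threshold by chance and the corrected p-value loses its stated meaning.

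**Working it through.** **Inputs**

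- Cluster-forming threshold Z > 2.3, corrected cluster p = 0.05 (Data analysis).
- Between-participant variance set to 0 in the group model (Data analysis).
- Group sizes for the check: 60 v 30 (one high-risk profile v low-risk) and 60 v 60 (one high-risk profile v the other, or intervention v no intervention among the 120 high-risk youths), from Participants.
- r = s_b² / s_w², between-participant over first-level variance. **Not given in the document.** Assumed range 0 to 4.

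**Step 1: the plan's own figure.** The nominal one-sided voxel rate at Z > 2.3 is 1 − Φ(2.3) = 0.0107. The cluster-level 0.05 cannot be reproduced, because image smoothness and search volume are not stated.

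**Step 2: the two standard errors.** For a difference between two group means:

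- fixed effects: SE² = s_w² (1/n1 + 1/n2)
- true: SE² = (s_w² + s_b²)(1/n1 + 1/n2)

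The ratio of true to assumed SE is √(1 + r). The group sizes cancel, so at a given r a larger sample does not reduce the problem. The same ratio applies to a single group mean.

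**Step 3: actual voxel rate.** Under the null, the fixed-effects Z has standard deviation √(1 + r), so the rate is 1 − Φ(2.3 / √(1 + r)).

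| r (assumed) | √(1 + r) | 2.3 / √(1 + r) | Voxel rate | Multiple of nominal |
|---|---|---|---|---|
| 0 | 1.000 | 2.300 | 1.07% | 1.0 |
| 0.25 | 1.118 | 2.057 | 2.0% | 1.9 |
| 0.5 | 1.225 | 1.878 | 3.0% | 2.8 |
| 1 | 1.414 | 1.626 | 5.2% | 4.8 |
| 2 | 1.732 | 1.328 | 9.2% | 8.6 |
| 4 | 2.236 | 1.029 | 15.2% | 14 |

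**Step 4: simulation.** With 100,000 runs per setting and r = 0, 0.5, 1, 2 and 4, the fixed-effects test agreed with the formula. At r = 1 it gave 5.3% (60 v 30) and 5.2% (60 v 60). A test using the observed between-participant variance gave 1.0% to 1.1% at every r in both settings. That comparator was a pooled two-sample t statistic converted to Z, not FLAME itself. It shows that restoring the missing variance restores the nominal voxel rate at Z > 2.3.

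**The case against.** Several points on the other side stand and limit the scope.

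- **The named group test is elsewhere.** The Statistical analyses section assigns the group comparisons to ANCOVAs on ROI scores, whose residual variance lies between participants. Cortical thickness and VBM do not use FLAME either. A reader might infer that all three objectives lose their inferential basis; the document does not support that. The defect is confined to the voxelwise fMRI maps, which may be the exploratory arm.
- **No second-level contrast is listed.** The Data analysis section does not say which groups the voxelwise model compares. It may produce only group activation maps, so an effect on the intervention comparison in particular is not shown. The variance error applies to either kind of map.
- **Tractography.** A reader might infer that the error carries into the diffusion results. The text does not say whether the age-trend regions come from the voxelwise maps or the ROI analysis. Even in the first case, a falsely chosen region makes a tract less relevant but does not by itself inflate the error of a group comparison on diffusion measures.
- **Generalisability.** The Discussion's claim to "test the generalizability of our sample and findings to the general population" looks like a direct contradiction. It concerns how well the imaging subsample represents the larger trial in which it is embedded, not voxelwise inference, so the point does not rest on it.
- **The threshold.** One might add that Z > 2.3 is itself too lenient. Nothing calculated here shows that: the voxel rate is nominal at that threshold once the variance is estimated.

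One defence does not stand. Fixed effects would be proper for combining sessions within a person, but the sentence names the group level, the inferential threshold follows directly, and no higher level is described. Nor is this a detail left to a fuller plan, since the article states the choice outright.

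**Conclusion.** The sentence is wrong as written for inference beyond the youths scanned. The nominal voxel rate holds only if r = 0, that is, if participants do not differ in true activation. At r = 0.25 the rate has nearly doubled, and across r = 0.5 to 4 it is about 3 to 14 times nominal. The direction is certain for any r above zero. The size rests on the assumed r, which will vary across the brain, so the figures illustrate and do not measure this study's error rate. The stated cluster-corrected p = 0.05 is therefore unsupported, although by how much it is exceeded cannot be calculated from the document.

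**What to change.** Replace the fixed-effects sentence in Data analysis with one of the following:

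- a mixed-effects group analysis that estimates the between-participant variance (FLAME 1 or FLAME 1+2); or
- permutation inference across participants on the subject-level contrast maps.

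State that fixed effects are used only to combine runs or sessions within a participant. Because each participant is scanned three times, also state how visits enter the group model: reduce them to within-participant summaries, for example change or slope maps, before the group level. Say as well whether the age-trend regions used for tractography come from these maps or from the ROI analysis.

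The cost is a software setting, a few sentences, the set-up of the within-participant summaries and more computing time. Fewer clusters will reach significance.

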#### Statistical analyses

The main objectives of the statistical analyses will be to characterize differences for fMRI, cortical thickness, VBM, DWI and behavioral measures between high (SS and IMP) and low-risk youth, binge drinkers and non-drinker trajectory, and those assigned to the intervention or not (with and without exposure to alcohol) over time. Two- and three-way repeated measures analyses of covariance (ANCOVA) will be performed based on region of interest (ROI) scores with covariates such as age, socioeconomic status, pubertal stage, IQ, and other drug use. For cortical thickness and VBM only a-priori defined ROI will be used (i.e., prefrontal lobes, basal ganglia, limbic brain regions and corpus callosum), as previous studies have shown that alcohol affects these regions. For fMRI, we will conduct both exploratory and ROI analyses, and for the DWI data, the regions showing linear age trends in the fMRI analysis will be used as start/finish points for probabilistic tractography.

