**Methods:**

A subsample of 120 youth at high risk for substance misuse and 30 low-risk youth will be recruited from the Co-Venture trial (Montreal, Canada) to take part in this 5-year follow-up neuroimaging study. The Co-Venture trial is a community-based cluster-randomised trial evaluating the effectiveness of school-based personality-targeted interventions on substance use and cognitive outcomes involving approximately 3800 Grade 7 youths. Half of the 120 high-risk participants will have received the preventative intervention program. Cognitive tasks and structural and functional neuroimaging scans will be conducted at baseline, and at 24- and 48-month follow-up. Two functional paradigms will be used: the Stop-Signal Task to measure motor inhibitory control and a modified version of the Monetary Incentive Delay Task to evaluate reward processing.

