## Methods

### Objectives and hypotheses

In 2011, the Co-Venture Trial was funded by the Canadian Institutes of Health Research (CIHR) to test the 4-year impact of the Preventure programme on delaying early onset drinking and binge drinking in students as well as long-term addiction outcomes. A subsequent CIHR grant was awarded for the Neuroventure study, allowing us to add longitudinal neuroimaging measures to test the following objectives/hypotheses:Compare high-risk (IMP and SS) and low-risk youth on measures of brain structure and function to quantify neurocognitive endophenotypes of these two risk profiles prior to exposure to alcohol in adolescence. We expect to observe impaired fronto-striatal connectivity and function during response inhibition in IMP as well as altered function of frontal and sub-cortical regions (i.e., basal ganglia and ventral striatum) during reward anticipation in SS.Measure the correlates of adolescent drinking and binge drinking on the development of brain structure and function in adolescence, controlling for baseline differences in personality, cognitive profiles, and neural measures that are implicated in the predisposition to early onset alcohol misuse. By comparing youth who take up drinking to those who do not (regardless of intervention status), we will test the extent to which binge drinking trajectories are associated with delayed or altered development of fronto-striatal and fronto-limbic networks that mediate response inhibition and anticipation of reward/punishment. Three hypotheses will be examined. i) Global effects: abnormalities will be observed systematically across all measures of brain function and structure, ii) Developmental specificity: alcohol-induced abnormalities will be specific to regions and cognitive processes that are maturing in adolescence, and iii) Interaction effect: alcohol will exacerbate the abnormalities shown to characterize each high-risk group at baseline.Test causal hypotheses by testing whether delaying drinking (through the Preventure Programme) can produce observable protective effects on structural and functional brain development. By comparing high-risk youth who received intervention to those who did not, we will estimate an intervention effect on structural and functional brain outcomes, which again might be expressed globally across the brain, or more specifically in those areas developing during adolescence or most abnormal in high-risk groups (as revealed in objective 1).

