#### Procedure

Eligible students will be invited to attend three identical scanning sessions over a 5-year period: the first session during the baseline year of the Co-Venture Trial (for intervention schools, this would refer to the period prior to when intervention sessions are run), and second and third session 24 and 48 months later, respectively (Grade 9 and 11). Participants will undergo a 65-min structural and functional neuroimaging assessment, and will complete a 2-h battery of neuropsychological tasks post-scan. In addition, participants will be assessed on substance use, global IQ and behavioral measures annually for 4 years post intervention through the Co-Venture Trial.

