## Discussion

Imaging studies using different modalities have consistently reported that alcohol use during adolescence is associated with abnormalities in brain structure, function and connectivity [72]. However, the critical question of whether these anomalies are consequences of alcohol abuse or preexisting vulnerability factors for early use and misuse remains unanswered in the literature. This prospective, intervention study will allow us to identify brain, cognitive, and behavioral factors that precede (and predispose to) adolescent alcohol misuse versus factors that are consequential to such use. Moreover, this unique study will enable us to test whether an early alcohol prevention intervention produces protective effects on brain structure, function and connectivity in adolescents, while controlling for potential pre-morbid factors associated with a susceptibility to early onset drinking. By focusing on the neural correlates of adolescents at risk for harmful drinking, and by examining the effects of adolescent drinking and binge drinking on the development of brain structure and function, the study will extend the knowledge gained from other large-scale studies (e.g., European Commission FP6-Health www.imagen-europe.com and National Institutes of Health’s “Longitudinal Studies on the Impact of Adolescent Drinking on the Adolescent Brain”). Perhaps more importantly, this innovative experimental design will allow us to test the causal relationship between early alcohol exposure and neurocognitive and addiction outcomes by showing that delaying drinking in those most at-risk protects normal neurocognitive development.

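### The analysis section splits the intervention comparison by later alcohol exposure, while Objective 3 states it unsplit; only the unsplit form, with pre-intervention covariates, can serve as the causal test

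*Protocol article*

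**What the plan says.** The protocol article gives the intervention comparison in two forms.

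- Statistical analyses names the third contrast as "those assigned to the intervention or not (with and without exposure to alcohol) over time". The models are two- and three-way repeated measures ANCOVAs on region-of-interest scores, "with covariates such as age, socioeconomic status, pubertal stage, IQ, and other drug use". This one open list serves the risk-group, drinking-trajectory and intervention contrasts, and the time at which each covariate is measured is not given.
- Objectives and hypotheses, Objective 3, has no split: "By comparing high-risk youth who received intervention to those who did not, we will estimate an intervention effect on structural and functional brain outcomes". Its stated purpose is "testing whether delaying drinking (through the Preventure Programme) can produce observable protective effects on structural and functional brain development".

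Three other statements bear on the covariates. The abstract describes the parent trial as "evaluating the effectiveness of school-based personality-targeted interventions on substance use and cognitive outcomes". Under Procedure, "participants will be assessed on substance use, global IQ and behavioral measures annually for 4 years post intervention". The Discussion says the intervention test will be made "while controlling for potential pre-morbid factors associated with a susceptibility to early onset drinking".

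**The concern.** Objective 3 is presented as the causal part of the study, and its strength comes from school-level random allocation. Drinking lies on the path from allocation to the brain. Splitting the arms by it does two things.

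1. It blocks the effect of interest. If the programme protects the brain by delaying drinking, drinkers compared with drinkers, and non-drinkers with non-drinkers, show none of that protection.
2. It makes the strata unlike. Non-drinkers in the intervention arm include youths who would have drunk without it; non-drinkers in the control arm do not. If whatever disposes a youth to drink is also related to the brain measures, the arms differ within strata even when nothing was caused. Objective 1 itself expects brain differences between risk groups before any alcohol exposure, so a shared cause is plausible on the plan's own terms.

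Other drug use raises the same problem if follow-up values enter the model, because substance use is an outcome of the parent trial. The case for IQ is weaker: cognition is also a parent-trial outcome, but nothing shows that the programme or drinking would shift IQ much.

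**Working it through.** The plan gives no figure for this comparison, so there is none to reproduce. The check asks what each form of the contrast returns under known truths.

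**Inputs from the article.** High-risk youth: 60 per arm (Participants). Binge drinking at 15 in high-SS and high-IMP youth: about 95% (Discussion). Reduction by the programme: 40 to 60% (Abstract; up to 50% in the section on the Preventure Programme).

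**Assumptions not in the article.** Binge drinking stands in for alcohol exposure. Liability to drink correlates ρ = 0.1 to 0.3 with a brain-vulnerability score. Baseline scan reliability is 0.7.

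**Step 1: removal of a real effect.** Suppose drinking lowers a brain measure by 0.5 SD and no trait is shared. With a 50% reduction, drinking is 95% in control and 0.95 × 0.5 = 47.5% with intervention.

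- Unsplit effect: 0.5 × (0.95 − 0.475) = 0.24 SD in favour of the intervention.
- Effect within drinkers, and within non-drinkers: 0.

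Now add a trait that raises drinking (log-odds 1 to 2 per SD) and lowers the measure by 0.2 to 0.3 SD per SD. In simulation the unsplit contrast stays near +0.24 SD. The split contrast becomes −0.08 to −0.17 SD in drinkers and −0.10 to −0.27 SD in non-drinkers. A true benefit then looks like harm.

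**Step 2: a spurious effect under the null.** Neither the programme nor alcohol affects the brain. Liability is standard normal, and a proportion p drinks, namely those above the threshold t. The mean vulnerability score is ρφ(t)/p in drinkers and −ρφ(t)/(1 − p) in non-drinkers.

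- Control, p = 0.95, φ(t) = 0.103: +0.109ρ in drinkers and −2.063ρ in non-drinkers.
- Intervention at a 50% reduction, p = 0.475, φ(t) = 0.398: +0.838ρ and −0.758ρ.

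Arm differences (intervention minus control):

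| Reduction | Drinkers | Non-drinkers |
|---|---|---|
| 40% | 0.581ρ | 1.149ρ |
| 50% | 0.730ρ | 1.304ρ |
| 60% | 0.893ρ | 1.449ρ |

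At ρ = 0.3 this is 0.17-0.27 SD in drinkers and 0.34-0.43 SD in non-drinkers. At ρ = 0.1 it is 0.06-0.09 and about 0.12-0.14 SD. Simulation agrees, and the unsplit difference is 0.00. The intervention arm has the higher vulnerability in both strata, so the bias runs against the programme. A trait related to the brain measure in the other direction would reverse it.

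**Step 3: allowing for the baseline scan.** Adjusting for a baseline measure of reliability 0.7 leaves roughly 1 − 0.7 = 0.3 of each gap. Over ρ = 0.1 to 0.3, simulation gives about 0.03-0.12 SD in non-drinkers and 0.02-0.07 SD in drinkers. The upper ends move by up to 0.02 according to whether the follow-up measure also carries measurement error. For a pure change score with a stable trait, the spurious difference is 0.00 in both strata.

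**Step 4: cell sizes.** At 95% and 47.5% of 60, control has 57 drinkers and 3 non-drinkers; intervention has 28.5 and 31.5. Power for a difference of 0.5 SD (two-sided 0.05) is 78% unsplit, 59% in drinkers and 13% in non-drinkers.

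**The case against.** The strongest reply is that the unsplit contrast is already planned. Objective 3 states it, an arm-by-time model would be its natural two-way form, and nothing calls the exposure split primary. This stands. A reader might infer that the randomised contrast as such is biased, and the article does not support that. The bias belongs to the split form.

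The covariates are a similar case. A reader might infer that follow-up drug use and IQ will be adjusted for. The annual reassessments show only that such values will exist. The Discussion speaks of pre-morbid factors, and Objective 2 of baseline cognitive profiles. Baseline values would cause no such bias.

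The size is also open to challenge. The 0.12-0.43 SD range describes one post-intervention measure, whereas the plan has repeated scans, the first before the intervention sessions. With that scan in the model the selection bias is much smaller, and it vanishes in change scores unless the trait alters the trajectory. This stands too. It does not rescue the split, because conditioning on drinking still removes any effect carried through it.

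Finally, the count of 3 control non-drinkers uses binge drinking at 15. The article gives no rate of alcohol exposure at the 24- or 48-month scans, so the count is an illustration.

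**Conclusion.** The point holds as a conflict between two sections with a clear statistical consequence. Followed as written, the exposure-split comparison cannot be the causal test of Objective 3. Its loss of any drinking-mediated effect needs no assumption about shared traits: under the illustrative 0.5 SD drinking effect, 0.24 SD becomes 0.

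The added selection bias does need a shared cause. Under the null, with ρ between 0.1 and 0.3, it is about 0.12-0.43 SD (non-drinkers) and 0.06-0.27 SD (drinkers) without a baseline measure. With a baseline scan of reliability 0.7 it is about 0.03-0.12 and 0.02-0.07 SD, and these smaller figures are closer to the planned design. Both ρ and the reliability are assumed.

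The covariate part is conditional: adjustment for other drug use would bias the contrast only if post-intervention values are used, and the same holds, more weakly, for IQ.

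**What to change.** Reconcile Objective 3 with Statistical analyses before the outcome data are analysed:

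- Name as the primary Objective 3 estimate the unsplit comparison by allocated arm among high-risk youth, as arm by time, adjusted for the baseline region-of-interest score.
- State that drug use and IQ enter this model only as pre-intervention values.
- Label any analysis by alcohol exposure, including mediation analysis, as secondary and dependent on assumptions about shared causes of drinking and brain measures.

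The change is to wording. The pre-intervention scan is already scheduled, and no new measurements are proposed. The price is that the exposure-stratified result can no longer be a headline finding.
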